## Abstract

**Background:**

Coronary artery disease (CAD) is accountable for more than 7 million deaths each year according to the World Health Organization (WHO). In a European population 80% of patients diagnosed with CAD are overweight and 31% are obese. Physical inactivity and overweight are major risk factors in CAD, thus central strategies in secondary prevention are increased physical activity and weight loss.

**Methods/Design:**

In a randomized controlled trial 70 participants with stable CAD, age 45–75, body mass index 28–40 kg/m^2^ and no diabetes are randomized (1:1) to 12 weeks of intensive exercise or weight loss both succeeded by a 40-week follow-up. The exercise protocol consist of supervised aerobic interval training (AIT) at 85-90% of VO_2_peak 3 times weekly for 12 weeks followed by supervised AIT twice weekly for 40 weeks. In the weight loss arm dieticians instruct the participants in a low energy diet (800–1000 kcal/day) for 12 weeks, followed by 40 weeks of weight maintenance combined with supervised AIT twice weekly. The primary endpoint of the study is change in coronary flow reserve after the first 12 weeks’ intervention. Secondary endpoints include cardiovascular, metabolic, inflammatory and anthropometric measures.

**Discussion:**

The study will compare the short and long-term effects of a protocol consisting of AIT alone or a rapid weight loss followed by AIT. Additionally, it will provide new insight in mechanisms behind the benefits of exercise and weight loss. We wish to contribute to the creation of effective secondary prevention and sustainable rehabilitation strategies in the large population of overweight and obese patients diagnosed with CAD.

**Trial registration:**

ClinicalTrials.gov:
NCT01724567

## Background

Coronary artery disease (CAD) is accountable for more than 7 million deaths each year according to the World Health Organization (WHO)
[1]. Overweight and physical inactivity are major risk factors in CAD. Weight loss through reduced calorie intake and improved fitness through increased physical activity are central strategies in both primary and secondary prevention. CAD mortality has decreased considerably during the last 30 years due to improved treatment, prevention and rehabilitation
[2]. However, due to the increased life expectancy the prevalence of CAD is increasing; thus, effective secondary prevention, optimal patient advice and sustainable rehabilitation programs are essential in decreasing morbidity and increasing quality of life in CAD.

### Benefits of exercise training on cardiovascular risk factors

Peak aerobic capacity (VO_2_peak) is a predictor of all-cause mortality in patients with CAD
[3]. Several smaller studies in patients with metabolic syndrome
[4], CAD
[5], congestive heart failure (CHF)
[6], hypertension
[7] and diabetes
[8] have shown that aerobic interval training (AIT) is superior to moderate continuous training in improving VO_2_peak and other cardiovascular risk markers such as endothelial function, glucose tolerance, hypertension and dyslipidemia. Furthermore, longer-term exercise training may even be superior to percutaneous coronary intervention (PCI) with stent implantation on event-free survival, anti-inflammatory effect and cost-effectiveness in selected patients with stable CAD
[9].

### Benefits of weight loss on cardiovascular risk factors

Obesity is a modifiable, independent risk factor of cardiovascular disease
[10]. In a European population 80% of the patients diagnosed with CAD are overweight (Body Mass Index (BMI) > 25 kg/m^2^) and 31% are obese (BMI > 30 kg/m^2^)
[11]. In overweight but otherwise healthy subjects, a low energy diet (LED), defined as 800 – 1000 kcal/day, resulted in a considerable weight loss with no apparent risk
[12]; however, there are no studies describing the use of LED in patients with CAD. The pan-European study DiOGenes used an LED to facilitate an initial weight loss of more than 8% of the original body weight in an overweight population, which resulted in a reduction of both cardiovascular
[13] and metabolic risk
[14]. A British study using a very low energy diet (600 kcal) to induce weight loss showed that insulin resistance and beta cell failure could be reversed in diabetic patients
[15]. Reduced heart rate variability (HRV) is an established marker of cardiovascular risk. In the COBRA study
[16], a 5% weight loss in postmenopausal obese women led to an increase in HRV.

A considerable challenge is to maintain a stable weight following the initial weight loss. According to the DiOGenes study, the most effective way to achieve this is ad libitum consumption of a diet with high protein content and low glycemic index carbohydrates
[17]. The effect of this diet prescription in CAD patients is not well described; however, the participants in the DiOGenes study obtained reductions in triglycerides and high sensitivity C-reactive protein (hsCRP) while HDL cholesterol was significantly increased after 26 weeks’ diet
[13].

### The effect of lifestyle changes

Large interventional studies aiming at weight reduction and improved fitness in overweight subjects have found a favorable effect on cardiometabolic risk following intervention
[18,19]. The recent look AHEAD trial showed improved fitness and glycemic control and a reduction in weight and cardiovascular risk factors in overweight patients with type II diabetes undergoing lifestyle intervention compared with diabetes support and education after one
[20] and four
[21] years’ intervention. Nonetheless, improvements were difficult to sustain over a prolonged period and there was no difference in cardiovascular morbidity and mortality after a median follow-up of 9.6 years
[22]. A Danish study from 2012 comparing endurance training with or without weight loss and weight loss obtained by calorie restriction in sedentary, moderately overweight but otherwise healthy young men found that loss of fat mass improved hepatic insulin sensitivity, while peripheral insulin sensitivity and VO_2_peak were improved only by endurance training
[23].

### Coronary flow reserve, weight loss and exercise

Coronary flow reserve (CFR), which is a measure of coronary microvascular function in the absence of significant stenosis, is reduced in individuals with diabetes
[24], obesity
[25] and CAD
[26]. CFR has been shown to be a predictor of poor prognosis and mortality in patients with known or suspected CAD even when the coronary arteries were normal
[27,28]. In CHF patients CFR has been shown to be positively correlated to VO_2_peak
[29]. Exercise training has been shown to improve CFR in patients with CAD
[30], while weight reduction following a multidisciplinary rehabilitation program resulted in improved CFR in overweight persons with no CAD
[25]. To our knowledge, there are no interventional studies in CAD patients comparing the effect of weight loss and exercise on CFR.

### Weight loss, exercise and insulin resistance

Insulin resistance is directly associated to CAD
[31]. Physical exercise and weight loss have been shown to improve insulin action
[19], which is considered an important mechanism behind the reduction in cardiovascular risk in CAD with lifestyle modification. Presence of abdominal adipose tissue particularly is associated with insulin resistance and thus cardiovascular risk via pathways involving adipokines, cytokines, ceramides and dysfunctional fatty acid composition
[32].

Incretin hormones, released from the small intestine, play an important role in insulin secretion and resistance. Incretin secretion is impaired in patients with diabetes and smaller reductions in secretion are seen in overweight and obese individuals with insulin resistance and impaired glucose tolerance
[33]. Incretin hormones facilitate the glucose uptake in the myocardium and are possibly associated with left ventricular function in CAD
[34]. This could imply that changes in incretin function in overweight individuals following weight loss play a role in changes in cardiac and endothelial function. Small studies have indicated that physical exercise could influence incretin secretion
[35], however, knowledge is limited regarding the effect of exercise and weight loss on incretin function as well as the metabolic and hormonal effect in adipose tissue.

### Rationale of the study

Several benefits from weight loss and exercise training on cardiovascular and diabetes risk factors have been described. Both LED and AIT could be first choice in secondary prevention in patients with CAD, yet a head-to-head comparison has not yet been performed. Thus, the primary objective of the CUT IT study is to investigate the effect of an effective weight loss protocol compared to 12 weeks of intensive AIT in overweight CAD patients. The primary endpoint is change in CFR and secondary endpoints describe the effect of the intervention on cardiovascular, metabolic and inflammatory risk markers. Secondary objectives are sustainability of the results during a 40-week follow-up period, containing AIT twice weekly or weight maintenance and AIT twice weekly.

## Methods/Design

### Study population

Participants were included in the study from September 2011 to April 2013. The study is on-going and the last participants will be evaluated in April 2014. We included 70 patients (Figure 
1) with stable CAD; age 45–75 years, BMI 28–40 kg/m^2^ not diagnosed with diabetes. Further inclusion and exclusion criteria are listed in Table 
1. The participants were found through the coronary rehabilitation unit at Bispebjerg University Hospital and a registry of coronary angiography, which comprises all angiographies performed in the Danish Capital Region. If the medical record did not reveal any exclusion criteria, a letter of invitation was sent with written information about the trial. People interested in participation were invited to a screening visit, conducted by a medical doctor connected to the study, where they received information about the study orally. To screen for certain exclusion criteria echocardiography and cardiopulmonary exercise test (CPET) including ECG were performed. Furthermore, blood samples were taken to screen for diabetes, kidney- and liver disease. If eligible and still interested the participant signed informed consent.

**Figure 1 F1:**
[figure not shown]
Study design and inclusion.

**Table 1 T1:** Inclusion and exclusion criteria

Inclusion criteria	Stable CAD (defined as previous MI, PCI, CABG > 6 months prior to inclusion or classic angina pectoris and positive angiogram/SPECT/CT-angiogram)
	Age 45–75 years
	BMI 28–40 kg/m^2^
Exclusion criteria	Known diabetes
	Diabetes diagnosed at screening (repeated fasting plasma glucose ≥ 7 mM or Hba1c > 7%)
	Severe or moderate valve disease
	Main stem stenosis
	Ejection Fraction < 35%
	Physical or mental disability - expected to prevent completion of intervention
	Severe COPD or asthma (FEV1 < 50% of expected)
	Active cancer
	Severe kidney (eGFR < 40 mL/hour) or severe liver disease
	Severe ischemia or arrhythmias during exercise test
	2. or 3. degree AV block, not protected by pacemaker
	Organised training more than 2 times a week prior to inclusion
	Significant weight loss or weight gain (> 5%) 3 month prior to inclusion

*Abbreviations*: *BMI* Body Mass Index, *CAD* Coronary Artery Disease, *COPD* Chronic Obstructive Pulmonary Disease, *FEV1* Forced Expiratory Volume the 1st second, *eGFR* estimated glomerular Filtration Rate, *MI* Myocardial Infarction, *PCI* Percutaneous Coronary Intervention, *CABG* Coronary Artery Bypass Graft.

### Randomization and stratification

The participants were consecutively enrolled during the inclusion period and randomized (1:1) into two groups:

(1) 12 weeks of AIT three times a week, followed by 40 weeks’ AIT twice weekly.

(2) 8–10 weeks’ LED followed by 2–4 weeks of transition to a high protein/low glycemic index diet and 40 weeks of weight loss maintenance and AIT twice weekly.

Randomization was stratified according to BMI (≤ 32.5; > 32.5). A third party unrelated to the study performed en bloc randomization with bloc size 2, 4 and 6 using Stata 11.1 software (StataCorp, [name]).

### Intervention

#### Aerobic interval training

The patients warm up at a moderate intensity for 10 minutes on a staircase (total of 73 steps, minimum 5 times up and down) or on an exercise bike, followed by high intensity interval training (85–90% of VO_2_peak as determined by CPET, Borg scale 17–18) on an exercise bike. The intervals are 1–4 minutes, with a total of 16 minutes, separated by active pauses of 1–3 minutes. The total duration of each training session is 38 minutes. Physiotherapists with experience in cardiac rehabilitation instruct the participants and supervise all training session. Training intensity is monitored using heart rate monitors, lactate measurements and the Borg Scale.

#### Low energy diet

The participants are instructed by experienced clinical dieticians to maintain an LED for 8–10 weeks. The LED consisted of soups, shakes, porridge and bars from the Cambridge Weight Plan (Northants, UK) 4 times a day, combined with a few additional vegetables, yoghurt and one litre of skimmed milk resulting in a total of 800–1000 kcal/day. The diet is designed to provide the participants with all necessary micro- and macronutrients and has previously been shown to be efficient in weight loss
[36]. The consultations with the dieticians are both individual and group sessions at study week 1, 2, 4, 6, 8 and 10. At study week 8 or 10 the participants are introduced to the maintenance diet.

#### Weight maintenance diet

The weight maintenance diet is a high protein/low glycemic index diet modified from the DiOGenes study
[17]. Taking into consideration that the participants have CAD the high protein diet was adapted to resemble the Mediterranean diet, which is recommended to heart patients
[2], thus the protein sources were mainly fish, poultry, egg, dairy, and vegetables. The transition to the maintenance diet is conducted during visits at week 8, 10 and 12 and hereafter the participants consult the dietician monthly.

### Baseline and follow-up examinations

All participants are examined at baseline, after 12 weeks and after a year (flowchart summarized in Figure 
1). Most examinations were performed at University Hospital of Bispebjerg, Department of Cardiology, except the MRI that was performed at University Hospital of Herlev and PET that was performed at Rigshospitalet. The primary endpoint is change in CFR following the first 12-weeks’ intervention. Coronary flow velocity (CFV) is measured using transthoracic Doppler echocardiography to determine the flow in the distal part of the left anterior descending (LAD) coronary artery. CFR is calculated as the ratio between CFV at rest and during hyperaemia induced by infusion of dipyridamole or adenosine. Cardiac positron emission tomography-computed tomography (PET/CT) is used as the “gold standard” to validate CFR in a sample of the population.

Secondary endpoints will provide cardiovascular and metabolic insight into the effects of exercise and weight loss:

#### Cardiovascular endpoints

• Aerobic exercise capacity assessed by VO_2_peak

• Systolic and diastolic function assessed by echocardiography at rest and during semi-supine exercise

• Heart rate variability and ischaemic burden assessed by 48 hours Holter monitoring

• Peripheral endothelial function assessed digitally using the Endopat2000
[37]

• Blood pressure

#### Metabolic and inflammatory endpoints

• Beta cell function, insulin production and response expressed as Matsuda-index
[8] and HOMA-index and assessed using a 3-hour oral glucose tolerance test (OGTT)

• Incretin hormone response measured during a 3-hour OGTT

• Non-esterified fatty acids response measured during the 3-hour OGTT

• Inflammatory markers: interleukin-6 (IL-6), tumour necrosis factor alpha (TNF-α), high sensitive C-reactive protein (hsCRP) and soluble urokinase plasminogen activating receptor (suPAR)

• Fasting triglycerides and lipoproteins

• Oxidized lipids, lipoprotein particle size and density distribution

• Adipokines

• Body composition assessed by anthropometry and dual X-ray absorptiometry (DEXA)

• Visceral, liver and ectopic muscle fat assessed by abdominal magnetic resonance imaging (MRI)

• Fatty acids composition, ceramides and cytokine mRNA expression in adipose tissue

#### Other parameters

• Physical activity assessed by accelerometer and International Physical Activity Questionnaire (IPAQ)

• Changes in diet assessed by a 3-day written diet record

• Anxiety and depression symptoms assessed by the Hospital Anxiety and Depression (HADS) questionnaire

### Statistics

The primary endpoint was CFR and we wished to be able to detect difference in change in CFR between groups of 10%, equal to a change in CFR of 0.24 assuming a baseline mean CFR of 2.4 in similar patient groups from our experience
[25,26,38]. Information on the expected standard deviation (SD) of the within individual change was not available and was therefore conservatively assumed to be 0.3. With power of 0.8 and two-sided significance level of 0.05, 26 patients should be included in each group. Anticipating 30% dropout, randomization of a total of 70 patients was chosen. Based on previous studies, this sample size is sufficient to detect relevant differences in endothelial function
[39,40], HRV
[41], Matsuda index
[8] and HOMA
[42]. With a SD of CFR of 0.6, this sample size will provide 80% power to detect a between group difference of 0.5 in CFR after the intervention.

Analyses will be by intention-to-treat whenever possible and care will be taken to encourage drop-outs to participate in follow-up examinations.

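### Seventy randomised with 30% dropout leaves 49 evaluable patients, not the 52 (26 per arm) that the power calculation requires

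*Protocol article*

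**What the plan says.** The primary endpoint is fixed in the section on baseline and follow-up examinations: "The primary endpoint is change in CFR following the first 12-weeks’ intervention". The Statistics section sets the target difference between groups at 10%, "equal to a change in CFR of 0.24 assuming a baseline mean CFR of 2.4". The SD of the within-individual change "was not available and was therefore conservatively assumed to be 0.3". From these inputs it concludes: "With power of 0.8 and two-sided significance level of 0.05, 26 patients should be included in each group". The dropout allowance follows directly: "Anticipating 30% dropout, randomization of a total of 70 patients was chosen". The document does not say how the allowance was applied.

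Allocation is 1:1 (Randomization and stratification), so 70 means 35 per arm. The Study population section confirms that recruitment ended at that number: "We included 70 patients".

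**The concern.** A dropout allowance exists so that the number left for the primary analysis still meets the power requirement. Here the section gives three figures (26 per group, 30% dropout, 70 in total), and they cannot all hold. Any two of them exclude the third.

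At stake is the planned 80% power for the primary comparison. The calculation has almost no slack, because 26 is the smallest whole number per group that reaches 80%. Any shortfall therefore takes power below target even if the assumed SD of 0.3 is right, and that SD was chosen without data. A reader who has to interpret a null result would take from this section that 80% power had been protected against a 30% loss. On the section's own inputs it was not.

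**Working it through.** **Inputs** (all from the Statistics section, except the 1:1 allocation, which is in Randomization and stratification): difference 0.24; SD of change 0.3; two-sided significance level 0.05; power 0.80; 26 per group; dropout 30%; 70 randomised.

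**Step 1: reproduce the 26 per group.** The standardised difference is 0.24/0.3 = 0.8. The two-sample t-test with 80% power at two-sided 0.05 needs 25.52 per group, so 26. The stated figure is reproduced exactly. The normal approximation rounds up to 25, so the t-test is the method consistent with the document. Power by t-test is 79.1% with 25 per group and 80.7% with 26.

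**Step 2: apply the dropout allowance.** The number to randomise is N = (evaluable number required)/(1 − dropout).

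- Required evaluable: 2 × 26 = 52.
- N = 52/(1 − 0.30) = 74.3, so 75. By arm, 26/0.7 = 37.1, so 38 per arm and 76 in total.
- The stated 70 is 5 or 6 patients lower.

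**Step 3: see what 70 delivers.**

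- Evaluable after 30% loss: 70 × 0.70 = 49, that is, 24 and 25 per arm, or 3 fewer than 52.
- Largest loss that keeps 52: 70 − 52 = 18 patients, and 18/70 = 25.7%. The anticipated loss is 0.30 × 70 = 21 patients.

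**Step 4: consequence for power** (t-test, difference 0.24, SD 0.3).

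| Evaluable per arm | Power |
|---|---|
| 26 / 26 | 80.7% |
| 25 / 25 | 79.1% |
| 24 / 25 | 78.3% |

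The difference detectable with 80% power at 24/25 is 0.245 instead of 0.24. As a rough check, scaling by the square root of the sample size gives 0.24 × √(25.52/24.5) = 0.245.

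**Step 5: alternative routes to 70.** Multiplying instead of dividing gives 52 × 1.3 = 67.6, so 68, which is near 70 but does not reproduce it. Starting from the normal-approximation figure of 25 per group gives 50/0.7 = 71.4, so 72, which is also above 70 and conflicts with the stated 26. Neither route yields 70. Use of the multiplying formula is only a possible explanation, and nothing below depends on it.

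**Step 6: the section's other power statement.** A difference of 0.5 in CFR with SD 0.6 needs 23.6, so 24, per group by t-test. With 49 evaluable (24.5 per arm on average) power is 81.5%, so that statement survives a 30% loss.

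**The case against.** The strongest reply is that dropout need not mean a missing primary outcome. The Statistics section plans intention-to-treat analysis where possible and intends to encourage drop-outs to attend follow-up examinations. Bringing back 3 of the 21 anticipated drop-outs for the 12-week CFR would restore 52. Nor does the section say whether the 30% refers to week 12 or to the full 52 weeks. If it covers the whole trial, loss by week 12 could be lower, and anything up to 18 patients would be covered.

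Both points are fair, and they make the figure of 49 conditional. They do not reconcile the numbers. The allowance is there to cover patients lost to the primary analysis, and the document builds neither retrieval nor a lower loss at week 12 into its calculation. Had drop-outs been expected to supply the 12-week measurement, no 30% allowance would have been needed.

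It can also be said that the effect is very small. By the normal approximation, power at 24.5 per arm is 80.0%, and a change of under two points is minor beside an SD assumed without data. The smallness stands. The normal approximation does not rescue the figure, because it would have led to 25 per group rather than the stated 26. Finally, the section never states in so many words that power is 80% at 30% dropout. That is correct, but it is the plain implication of giving a required number and then an allowance for loss.

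**Conclusion.** The concern holds. The 26 per group is correct for its inputs, but 70 randomised does not deliver it at the anticipated dropout. The shortfall is 3 evaluable patients (49 against 52). Power is 78.3% against the planned 80%, and the detectable difference is 0.245 against 0.24.

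These consequences assume that all 30% lack the 12-week CFR, that the SD of change is 0.3, and that the groups are compared on unadjusted change, as the calculation implies. The conflict between 26 per group, 30% and 70 does not depend on the SD. The error does not threaten the trial, but it sits in the justification for the primary endpoint and should be corrected.

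**What to change.** Recruitment has ended at 70, so no patients need be added. Replace the sentence on dropout with one of two statements:

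- 70 randomised allows for about 25% of patients lacking the 12-week CFR measurement while keeping 26 per arm; or
- with 30% of patients lacking that measurement, 49 would be evaluable, giving about 78% power for a difference of 0.24 at an SD of 0.3.

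Whichever is used, say that the percentage refers to loss of the 12-week measurement. Later reports should not state or imply 80% power at 30% dropout for the unadjusted comparison of change. The cost is one sentence and a slightly less favourable figure; design, conduct and analysis are unchanged.
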